When older people that are chronically ill undergo treatment for an acute illness or hospital treatment, they often recover for weeks or months in intermediate- or short-term care facilities that provide basic nursing care [13]. In Sweden, this type of care can be provided in a short-term care unit, a residential setting, or a hospital (for intermediate care). Short-term care can also include support for older people, when they are in frail conditions and are waiting for care-home placement, undergoing rehabilitation, require recurrent relief for family members that are informal caregivers, and even when they require end-of-life care [14, 15]. Although thousands of older people are admitted yearly to Swedish short-term care units, there is little knowledge about the content of care and the effects on individual health, functioning, and quality of life [14, 15]. We also lack knowledge on how caretakers perceive the quality of care that they deliver. The scarcity of empirical studies on short-term care might be related to the expected methodological and ethical problems. For example, problems may be caused by the short care interval (individuals are admitted for only a few weeks), the frail state of older individuals, and the complex care organization. It has been suggested that conducting research in a short-term care context poses challenges related to obtaining informed consent, achieving sufficient power in intervention studies, and controlling for confounding factors, such as the different skill mixes and staffing levels in various care units [16]. In summary, there is an urgent need for new knowledge concerning the content, quality, and effects of short-term care for older people.

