## Methods

### Aims and research questions

The overall aims of this multidisciplinary, multicenter project are (*i*) to describe and analyze relationships between oral health and oral health-related quality of life (HRQoL), swallowing ability, eating ability, and nutritional risk for older individuals admitted to short-term care; (*ii*) to compare the perceptions reported by older individuals and staff on care quality related to oral hygiene and eating; and (*iii*) to study the feasibility and effects of a training program for older people that exhibit dysphagia, but have different diagnoses.

The research questions we will address are:What is the state of oral health among the older people admitted to short-term care?What is the state of swallowing ability among the older people admitted to short-term care?How do the older people admitted to short-term care describe their oral health and their oral HRQoL?How do the older people admitted to short-term care describe the quality of their oral care?How do staff members in the corresponding short-term care unit describe the quality of oral care delivered?Which factors impact the perceptions of care quality held by older individuals and the staff?What are the differences and similarities between older individuals and the staff in their perceptions of care quality?How does systematic training with an oral screen device for 5 weeks affect impaired swallowing function?How do older people admitted to short-term care describe their swallowing-related QoL?Is there any correlation between oral health, eating ability, and swallowing ability in older people admitted to short-term care?

This project will provide data for three doctoral theses; one student is a registered nurse, RN (MA); one is a registered dental hygienist, RDH (SK); and one is a speech-language pathologist, SLP (PH). Detailed descriptions of the specific aims and research questions for each doctoral project will be presented with the results in separate articles.

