### Design and setting

The SOFIA project consists of two main parts; part 1 is a descriptive, cross-sectional study (aims *i* and *ii*), and part 2 is a cluster randomized, controlled trial (aim *iii*).

Data collection will take place in 32 short-term care units, located in five Swedish counties, in both rural and urban areas. The short-term care units are diverse in organization and staffing; they may be one section of a care home or an independent short-term care unit.

Participating short-term care units will be selected, based on informed consent from the heads of social welfare services and unit managers; the number of beds; the estimated number of discharges per month; and the geographic location. The sample in part 1 will comprise approximately 400 older participants. All participants will be assessed at baseline, and participants that exhibit low swallowing capacity (i.e., <10 ml/s) will be asked to participate in the interventional part of the study (part 2). In part 2, participating older persons will, after informed consent, be randomized into either the intervention or the control group, based on where they were admitted for short-term care. In addition to the baseline assessments, all participants in part 2 will be assessed after the intervention is completed (5 weeks) and 6-months post-intervention. The follow-up assessments will be conducted at the study participant’s location (e.g., in the short-term care unit, in the individual’s own home, or in a care home, where the older person resides at that time).

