#### Care unit staff

All staff members working in the corresponding short-term care units will be eligible for study participation, including licensed practical nurses, nurse aides, registered nurses, occupational therapists, and managers.

All staff members will be informed about the study and will be provided with questionnaires at staff meetings. All questionnaires will be anonymized and mailed back to one of the researchers after review. A completed questionnaire will be taken to indicate informed consent. The manager of the short-term care unit will be instructed to remind the staff members to complete the questionnaire after two and four weeks.

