### Statistical methods

The statistical package, IBM/SPSS®, will be used to perform all data analyses. *P*-values less than 0.05 will be considered statistically significant. Descriptive statistics will be used to describe eating ability, oral health status, swallowing ability, quality of oral care, and swallowing-related QoL, among older individuals admitted to short-term care units. Descriptive statistics will also be used to describe the staffs’ perceptions of care quality. Univariate, bivariate, and multivariable regression (linear and logistic) analyses will be used to evaluate the associations between various dependent and independent variables. The Bonferroni correction will be used when multiple, pair-wise tests are performed on a single set of data, to reduce the chances of obtaining type I errors. Continuous variables will be presented as the mean value and standard deviation; categorical variables will be reported as the median and interquartile range. Differences between groups (e.g., intervention vs. control, older individuals vs. staff) will be assessed with independent sample t-tests (for continuous variables), chi-square tests (for categorical variables), and ANOVA or Kruskal-Wallis (for more than 2 groups).

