### Measurement tools

The minimal eating observation and nutrition form - version II (MEONF-II) [23, 24] is an easy-to-use, rapid, sensitive, screening tool that allows substituting of body mass index (BMI) with calf circumference, which increases its usability in this context, for assessing the risk of undernutrition. However, completing the form might be time-consuming for the nursing staff, and it requires a certain degree of familiarity with the older person.

The revised oral assessment guide (ROAG) [25, 26] is a systematic assessment tool for detecting problems related to teeth and dentures in older individuals. It was designed to be used by nursing staff, and it is well-documented in Sweden, because it is included in Senior Alert, the national registry of quality in geriatric care [27]. However, the assessment is performed solely with a mouth mirror and flashlight, not in a dental clinic.

The SCT [18] is a simple, easy-to use screening test for determining the risk of dysphagia in a non-hospital context. The SCT is a feasible tool for evaluating training paradigms for treating dysphagia [8]. The SCT requires an evaluation of age as a covariate, when performing data analysis.

Several self-assessment questionnaires (Table 1) will be used in the present study to evaluate QoL related to different health areas, including: the OHIP-14 [28, 29], the QPP-patient [19, 20], and the SWAL-QOL [30, 31]. These questionnaires will contribute multifaceted information from the perspectives of older individuals. The results will guide further improvements in QoL in the short-term care context. However, answering questionnaires might be exhausting for older people. Therefore, there might be a risk of bias, if older individuals require support in reading and interpreting the questions. However, this type of support might lead to more accurate responses and fewer drop-outs.

The QPP-staff is a modified version of the QPP-patient questionnaire [19, 20]. The QPP-staff will provide important knowledge, from the perspective of nursing staff members, about the quality of care for older individuals in short-term care units. The challenges for this instrument are the risks of hasty, incomplete responses and drop-outs among the nursing staff members expected to complete the questionnaires. Due to the working situations of nursing staff, the many other tasks and priorities related to patient care might compromise their compliance with study requirements.

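### The older-individuals-versus-staff comparison is set as a pooled two-sample test although both groups come from the same 32 units; its error rate is off if the resident:staff mix or the gap varies by unit

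*Protocol article*

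**What the plan says.** The second overall aim (Aims and research questions) is "to compare the perceptions reported by older individuals and staff on care quality related to oral hygiene and eating". One research question asks "How do staff members in the corresponding short-term care unit describe the quality of oral care delivered"; a separate question asks how the two groups' perceptions differ or agree. On recruitment, the section Care unit staff says: "All staff members working in the corresponding short-term care units will be eligible for study participation". Design and setting adds: "Data collection will take place in 32 short-term care units, located in five Swedish counties", and of these units: "The short-term care units are diverse in organization and staffing".

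Statistical methods fixes the test: "Differences between groups (e.g., intervention vs. control, older individuals vs. staff) will be assessed with independent sample t-tests" for continuous variables and chi-square tests for categorical ones, at the 0.05 level. Regression is planned for associations in general. It is not assigned to this comparison, and no unit term is named. The Background lists, among the known difficulties of research in this setting, "controlling for confounding factors, such as the different skill mixes and staffing levels in various care units".

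**The concern.** An independent-samples test treats all residents as one sample and all staff as another, with every observation independent. Here residents and staff of one unit rate care in the same place, so their answers share whatever is good or poor about that unit. Two things can then go wrong.

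- **Unequal mix.** If a unit supplies a larger share of the residents than of the staff, its level of care enters the two means with different weights, and part of the pooled difference is a difference between units.
- **Varying gap.** If residents and staff disagree more in some units than in others, the true uncertainty depends on the 32 units. The test counts about 600 people.

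Nothing in the protocol equalises the mix. Residents enter by admission, eligibility and consent; staff enter by returning a questionnaire, and Measurement tools foresees "the risks of hasty, incomplete responses and drop-outs among the nursing staff members expected to complete the questionnaires". The Discussion expects the descriptions of oral care quality to be a basis for guidelines, so a perception gap that only reflects which units answered would matter.

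**Working it through.** **The plan's own figure.** The protocol gives no sample size or power calculation for this comparison. Its only calculated figure is 22 per group for part 2: 2 × (3/2.8)² × (2.241 + 0.842)² = 21.8, so 22. It reproduces (two-sided 2.5%, normal approximation) but has no bearing here.

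**Inputs from the protocol.** 32 units; about 400 older individuals and 200 staff (Abstract), on average 12.5 and 6.25 per unit; test level 5%.

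**Assumptions (not in the protocol).** Total variance 1; ICC 0.05–0.20; variance of the gap across units 0–0.20; several resident:staff mixes. The true mean gap is zero throughout.

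**Formula.** Let r_j and s_j be unit j's shares of all residents and all staff. The variance of the pooled difference is approximately

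error variance × (1/n_r + 1/n_s) + ICC × Σ(r_j − s_j)² + gap variance × Σ[(r_j + s_j)/2]²,

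where error variance = 1 − ICC − gap variance/4. The t-test uses about 1/n_r + 1/n_s, that is, a standard error of √(1/400 + 1/200) = 0.0866 SD.

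1. *Same ratio everywhere, constant gap, ICC 0.20.* The unit term vanishes. True SE = √(0.8 × 0.0075) = 0.0775, below 0.0866. Expected rejection 2.8%; simulated 3.1%. The test is conservative.
2. *Opposed mix* (half the units 18 residents and 3 staff, half 7 and 9; 400 and 192 in total), *constant gap, ICC 0.20.* Each unit's share difference is ±0.0294, so Σ(r_j − s_j)² = 32 × 0.0294² = 0.0276. True SE = √(0.8 × 0.00771 + 0.2 × 0.0276) = 0.108, against √0.00771 = 0.0878 in the test. Expected rejection 11.1%; simulated 12.0%.
3. *Same ratio, gap variance 0.20, ICC 0.10.* True SE = √(0.85 × 0.0075 + 0.20/32) = 0.112 against 0.0866. Expected rejection 13.1%; simulated 13.4%.

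Simulation (4000 runs per setting), rejection by the pooled t-test at nominal 5%:

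| Mix across units | Constant gap, ICC 0.05 / 0.10 / 0.20 | ICC 0.10, gap variance 0.10 / 0.20 |
|---|---|---|
| Same ratio | 4.8 / 3.5 / 3.1% | 8.9 / 13.4% |
| Randomly varying | 6.1 / 6.1 / 6.7% | 10.6 / 15.8% |
| Opposed | 7.0 / 8.3 / 12.0% | 12.4 / 17.1% |

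A one-sample t-test on the 32 unit-level resident-minus-staff differences rejected in 4.3–5.7% in every setting with a non-zero ICC.

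**Bias.** For a fixed set of units, suppose half score D higher and supply a share a of residents and b of staff. The pooled gap is then D(a − b) with no true gap. With D = 0.5 SD, a = 0.60, b = 0.40 it is 0.10 SD, or 0.10/0.0866 = 1.15 standard errors, and about 21% false positives. At 0.75 and 0.25 it is 0.25 SD and about 82%. Across repeated draws of units this averages to about zero unless the mix is related to unit quality. With an assumed correlation of 0.3–0.5 between staff response and unit quality, simulated mean bias was about 0.03–0.14 SD and rejection about 7–40%.

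**The case against.** A reader might infer that the pooled difference is biased as it stands, for instance because staff in better-run units return more forms. The documents do not support that. Measurement tools attributes hasty or missing staff responses to workload and competing tasks, not to unit quality. Care unit staff describes steps that favour response in every unit: distribution at staff meetings and manager reminders at two and four weeks. Without a relation between response and quality, the fault lies in the error rate, and there is no systematic shift.

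A reader might also infer that the aim defines a within-unit comparison. The reference to the corresponding unit occurs in the question on how staff describe care and in staff eligibility. The comparison question asks only about older individuals and staff, so an overall contrast across the participating units is a fair reading. Even so, its standard error must reflect the units, and the independent-samples test does not do that.

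Three further points carry some weight. The care-quality items are four-point ratings with a not-applicable option, so single items may go to the chi-square test, which the normal-outcome simulation does not cover; the chi-square test assumes independence too. The comparison belongs to the descriptive part of the project and is not the randomised contrast. And the article is condensed. But it names this comparison and this test, so the point concerns a stated choice and does not turn on missing detail. The planned regressions and the unit conditions collected from managers are not tied to it.

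**Conclusion.** The point holds in conditional form. The stated test ignores the shared units, and its type I error is off when the resident:staff mix or the gap differs between units: about 6–18% in place of 5%, under assumed ICC 0.05–0.20 and gap variance 0–0.20. Bias of about 0.03–0.14 SD arises only if staff response is also related to unit quality (assumed correlation 0.3–0.5). With a constant ratio and a constant gap the test is about right or conservative. All sizes are illustrative, because the protocol gives no ICC, gap variance or unit mix. An unequal mix is to be expected from the way the two groups are recruited. The change is worth making before this comparison is analysed; it does not affect the part 2 contrast.

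**What to change.** For older individuals versus staff, replace the pooled test by a within-unit comparison that allows the gap to vary between units. Either of these serves:

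- an analysis of the unit-level resident-minus-staff differences, with its standard error taken from their spread across units;
- a linear or ordinal model with respondent type and unit, plus either a random unit-by-group term or standard errors clustered on unit.

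Respondent type plus a fixed unit effect with ordinary standard errors is not enough. It rejects in about 4–6% if the gap is constant, but in about 7–16% at gap variance 0.05–0.20; unit-level differences or clustered errors hold about 4–6%. Report the pooled difference as descriptive.

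Costs: units where only one side responded drop out of this comparison. The standard error may be slightly larger (with the randomly varying mix and a constant gap at ICC 0.05, 0.095 against 0.089 SD). Staff questionnaires are anonymized, so a unit code, which is not a personal identifier, must be on the forms. If forms already returned lack it, the within-unit analysis cannot be done for them, and the pooled result should be reported as descriptive only.

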### Sample size calculation

In study 2, the primary outcome variables will be the changes in swallowing capacity (based on the SCT), measured at the start and end of treatment, and at follow-up, 6 months later. The sample size calculation will be based on the assumption that the data will be normally distributed. To retain an overall type I error of 5%, the type I error will be set to 2.5% for the primary endpoint. Based on historical data, we assume that the standard deviation of the change in SCT level will be 3 ml/s. To detect a critical difference of 2.8 ml/s in swallowing capacity between the intervention and control groups with a power of 80% and type I error of 2.5%, a sample size of at least 22 subjects would be required to fulfill the study protocol in each group. The total number of subjects included must be somewhat higher, to compensate for drop-outs.

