### Methodological considerations

Methodological and ethical problems were previously reported as challenges that explained the lack of empirical studies conducted in the short-term care context [16]. Therefore, the present project includes several strategies to increase the probability of succeeding and to strengthen the results, as follows: (1) only participants with sufficient cognitive capacity are included; (2) older individuals in end-of-life care are excluded; (3) multiple short-term care units are included, housed in various settings and located in different parts of Sweden; (4) a cluster randomization trail design is implemented; (5) both clinical and self-reported assessments are considered; (6) the data collectors are professionals that hold relevant clinical experience in communicating with older individuals and assessing their oral health and swallowing ability; in addition the research team has experience in the care context, where the data will be collected.

By minimizing methodological and ethical challenges, our results, regarding oral health status, swallowing, eating ability, and nutritional risk, might not be representative of all older people in short-term care, e.g., individuals in the highest risk categories will not be included. Other methodological challenges might arise when performing the intervention study with late follow-up assessments (six months). These challenges include accessing information on where the participant is located at the time of the follow-up; managing the high risk of drop-out, due to mortality, in the study population; and recruiting for part 2 of the study. The latter problem is expected, because older people might have low motivation to participate in swallowing rehabilitation, due to fatigue, or because they have adapted to their situation and find no use in training [6].

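### The t-test named for the primary 6-month SCT change uses only people with a 6-month value, so the contrast is biased if loss follows 5-week SCT and differs between arms

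*Protocol article*

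**What the plan says.** For part 2, the protocol article's Sample size calculation section makes SCT change the primary outcome, "measured at the start and end of treatment, and at follow-up, 6 months later". It adds that "the type I error will be set to 2.5% for the primary endpoint".

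The Statistical methods section states that group differences "will be assessed with independent sample t-tests (for continuous variables", and gives intervention versus control as an example. Regression appears with a different purpose: "Univariate, bivariate, and multivariable regression (linear and logistic) analyses will be used to evaluate the associations between various dependent and independent variables". No method for the arm contrast combines the two follow-up visits.

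Under Methodological considerations, the difficulties listed for the 6-month assessment include finding out where participants then live and "managing the high risk of drop-out, due to mortality, in the study population".

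Two responses to loss are stated. The Sample size calculation section says: "The total number of subjects included must be somewhat higher, to compensate for drop-outs". Design and setting provides for follow-up in the care unit, the participant's own home or a care home.

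Two other statements bear on the point. Table 1 schedules the SCT at baseline, 5 weeks and 6 months, and scores a failed teaspoon test as 0 ml/s. Measurement tools says that SCT analyses need age considered as a covariate.

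**The concern.** An independent-samples t-test on 6-month change needs a 6-month value from each person. As stated, it compares those still alive, located and willing at 6 months. The protocol expects that group to be depleted, chiefly by death. Its Background links impaired oral health, nutrition and eating ability to pneumonia and other infections, so loss related to swallowing is plausible.

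If so, the 6-month result describes the people who remain rather than those allocated. The error can go either way. If poor swallowers are lost under the same rule in both arms and training works, more controls are lost and the effect is understated. If poor responders are lost mainly from the training arm, it is overstated. Enrolling more people restores numbers but leaves either distortion in place. Many of those lost will have a 5-week SCT that is informative about their missing value, and the 6-month t-test ignores it.

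**Working it through.** **Inputs.** From Sample size calculation: SD of change 3 ml/s, difference 2.8 ml/s, power 80%, type I error 2.5%, 22 per group. Assumed, because the documents give none: loss by 6 months 15–40%; log-odds of loss 0.7–1.5 per SD of worse 5-week change; correlation ρ of 5-week and 6-month change 0.5–0.7; a true difference of 2.8 at both visits.

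**1. The plan's own figure.** With a two-sided 2.5% level and the normal approximation, n = 2(2.241 + 0.842)² × (3/2.8)² = 2 × 9.505 × 1.148 = 21.8, so 22 per group. The plan's figure is reproduced. These 22 are completers. To keep them, enrolment per group would be 22/0.8 → 28, 22/0.7 → 32 or 22/0.6 → 37 at 20%, 30% or 40% loss. That protects power only.

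**2. Bias formula.** Both changes have SD 3, so the slope of 6-month on 5-week change within an arm is ρ. If loss depends on 5-week change, the mean 6-month change of those retained is shifted by ρ × s, where s is the shift in their mean 5-week change. The completer contrast is therefore

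2.8 + ρ × (s_training − s_control).

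It is unbiased when the two shifts are equal, including when both are zero.

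**3. Results** (simulation, 400,000 people per arm, logistic loss on 5-week change):

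| Loss mechanism | Range over the assumptions | 30% loss, slope 1, ρ = 0.7 |
|---|---|---|
| Same function in both arms | 2.30–2.73 (−18% to −2%) | 2.52 (−10%) |
| Follows SCT in training arm only, equal overall loss | 2.96–3.69 (+6% to +32%) | 3.32 (+19%) |
| Either mechanism, 5-week value used in the estimate | 2.79–2.82 | – |

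Check of the last column by integrating the logistic loss curve over the normal distribution in each arm:
- Same function: loss is 38% in controls and 22% in the training arm, with s_control = 0.95 and s_training = 0.57. Then 2.8 + 0.7 × (0.57 − 0.95) = 2.53.
- Training arm only: s_training = 0.76 and s_control = 0. Then 2.8 + 0.7 × 0.76 = 3.33.

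Both agree with the simulation to 0.01.

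**4. Other mechanisms** (20–40% loss, slope 1, 200,000 per arm). If loss follows SCT in controls only, the estimate is about 2.1–2.5. If rate and dependence are equal in both arms, it is within 0.03 of 2.8. The same holds if loss does not depend on SCT at all.

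The first row of the table does not contradict the equal-rate result. Under one common function, an effective training improves 5-week SCT and so lowers loss in the training arm. The rates then differ.

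**5. Scale.** With 22 completers per group the standard error is 3 × √(2/22) = 0.90 ml/s. The central biases, −0.28 and +0.52, are about 0.3 and 0.6 of a standard error.

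**The case against.** **A t-test does not fix who is analysed.** It could be run on imputed data, the sentence covers the whole project, and a full analysis plan may deal with missing values. This stands in part: the lack of an imputation section is no finding. The point rests instead on a stated test set beside a stated drop-out risk, for a primary variable.

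**Adjusted analyses are foreseen.** Age is named as a covariate for the SCT, and multivariable linear regression is available. That weakens any claim that an unadjusted comparison is all that is intended. But regression is assigned to associations, and a regression on 6-month change alone also needs the 6-month value.

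**Stronger readings that fail.**
- A reader might infer that the protocol expects drop-out from low motivation, because it says that "older people might have low motivation to participate in swallowing rehabilitation, due to fatigue". In context that explains expected difficulty in recruiting for part 2. The drop-out cause it names is mortality.
- A reader might infer that more enrolment is the only answer to loss. Follow-up at the participant's location is another.
- A reader might infer that the 5-week data are discarded. They are unused only in the 6-month contrast.
- A reader might infer that people who swallow too poorly to be tested go missing. The 0 ml/s rule in Table 1 keeps those who fail the teaspoon test in the data.

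**The size is assumed.** This stands. Recovery of about 2.8 is also built in, because the simulated loss depended only on the observed 5-week change. It shows what the model can do under that condition and is not evidence about this trial.

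**A mixed model does not settle deaths.** This stands too. Under missing at random it implicitly gives the dead a 6-month SCT, so their treatment must be stated separately.

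**Conclusion.** The point holds in conditional form. The test stated for the part 2 contrast, applied to the primary 6-month SCT change, uses only people with a 6-month value, at a visit where the protocol itself expects high loss. The contrast is biased if loss is related to 5-week SCT and differs between arms in rate or mechanism. Under the two main mechanisms and the assumed ranges, a true 2.8 ml/s is estimated as about 2.3–3.7 ml/s; loss following SCT in controls only could take it to about 2.1.

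A reader might infer that the 6-month result will be biased. The documents do not support that, since they give no drop-out rate, correlation or mechanism. If loss is unrelated to SCT, or has equal rate and dependence in both arms, there is essentially no bias and only precision is lost. The 5-week comparison is not affected by loss after 5 weeks. The change should be made, with medium confidence in its practical size.

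**What to change.** For the part 2 primary outcome, replace the separate t-tests with one linear mixed model of SCT at 5 weeks and 6 months (SPSS MIXED, within the package already named):
- all allocated participants with any post-baseline SCT;
- arm, visit and arm-by-visit as fixed effects;
- baseline SCT and age as covariates;
- a random effect for care unit, because allocation is by unit, and correlation between a person's two visits.

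Read both arm contrasts from this model. State that the 6-month contrast treats deaths as missing, report deaths by arm, and add one sensitivity analysis that ranks death below an SCT of 0.

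The cost is analysis wording and slightly more analysis work, with no new data, visits or participants. The model assumes data are missing at random, which is weaker than what the completer t-test needs. It does not recover people with no post-baseline SCT.
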